### Interim analyses {21b}

We formalized one interim analysis with the ability to stop for superiority or futility, which will be conducted at 57% of the required number of events. The following stopping rules are defined (Table 2):

**Table 2 Tab2:** Pre-determined stopping rules

Analysis	% of events	Futility		Superiority	
		*Z*	*Beta-spend*	*Z*	*Alpha-spend*
**I**	57%	0.36	0.0370	2.60	0.0046
**II**	100%	1.99	0.1630	1.99	0.0204
**Total**			**0.20**		**0.025**

The pre-specified stopping rule for efficacy is be based on the Lan-DeMets procedure with O’Brien-Fleming alpha-spending function with an asymmetric two-sided group sequential design with 80% power and 2.5% type I error. Upper bound spending computations assumed that the trial will continue if the lower bound is crossed (i.e., non-binding). At the interim analysis, a standardized likelihood ratio test statistic is calculated and compared to the *Z*-values provided in the table above. As soon as the test-statistic falls outside either the futility or superiority boundary, the study may be stopped for either superiority or futility.

In case enrolment is slow or a stopping rule is crossed early, the trial is likely to be terminated before all 171 patients have been enrolled. If treatment is futile, the trial can be stopped on average after 28.0 months since first enrolled patient with an average sample size of 137 patients. In this scenario, the probability for individual patients to remain in the trial for 18 months or more is 11.3% and to complete 24 months is 1.8%.

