#### Sample size {14}

The sample size calculation for this event-driven trial is based on the primary efficacy end point death of any cause or respiratory insufficiency. The trial continues until the required number of events is reached or until 24 months after the last enrolled patient, whichever comes first. In the meta-analysis of lithium carbonate among patients homozygous for the C-allele at SNP rs12608932 in *UNC13A*, we found a crude hazard ratio (HR) of 0.43 and an adjusted HR of 0.30 (active vs. placebo) [8]. Due to the relatively small sample size of the meta-analysis (*n* = 46), we assumed a conservative hazard ratio of 0.50. With the use of a one-sided test at the 0.0250 significance level, the trial would have 80% power if it continued until 72 events occurred in the combined trial groups. We specified one pre-specified stopping rule for efficacy based on the Lan- DeMets procedure with O’Brien-Fleming alpha-spending function when 41 events occur (non-binding).

We used a simulation-based approach to estimate the event probability during follow-up and the required sample size. We assumed that 14.21% of the patients will be homozygous for the C-allele at SNP rs12608932 in *UNC13A*. With a planned maximum enrolment rate of 5–6 patients per month, enrolment of 171 patients (114 on active treatment and 57 on placebo) resulted in 72 events within 48 months since first enrolled patient for 99.5% of our simulated trials.

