#### General methods

The primary endpoint hypothesis tests will be 2-sided with a significance level of *α* = 0.05. Secondary endpoints will be considered exploratory, presented with 95% confidence intervals and without inferential statements. For each analysis, all available data (from first date of randomization to last follow-up) will be used.

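### Table 2's interim efficacy boundary (Z = 2.60, 0.0046 spent) is not the one produced by the Lan-DeMets O'Brien-Fleming function that the text names (Z = 2.75, 0.0030 spent)

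*Protocol article*

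**What the plan says.** The method is named in two places. Sample size {14} sets the error rate ("With the use of a one-sided test at the 0.0250 significance level") and places the single efficacy look at 41 of 72 events ("DeMets procedure with O’Brien-Fleming alpha-spending function when 41 events occur (non-binding"). Interim analyses {21b} repeats the method ("The pre-specified stopping rule for efficacy is be based on the Lan-DeMets procedure with O’Brien-Fleming alpha-spending function"), gives the timing ("which will be conducted at 57% of the required number of events") and describes the design ("with an asymmetric two-sided group sequential design with 80% power and 2.5% type I error"). It adds that the efficacy bound was computed with futility treated as non-binding.

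Table 2 in the same section then prints the boundaries:

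| Analysis | Events | Futility Z | Beta spent | Superiority Z | Alpha spent |
|---|---|---|---|---|---|
| I | 57% | 0.36 | 0.0370 | 2.60 | 0.0046 |
| II | 100% | 1.99 | 0.1630 | 1.99 | 0.0204 |
| Total | | | 0.20 | | 0.025 |

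The text sends the analyst to these numbers: "a standardized likelihood ratio test statistic is calculated and compared to the *Z*-values provided in the table above".

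**The concern.** A spending function, an error rate and an information fraction together fix the boundary, so Table 2 should follow from the text. It does not. The interim alpha in the table is about one and a half times what the named function releases at that point.

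This boundary decides whether the trial may stop early and claim efficacy. A spending-function design also relies on the function to supply a new boundary when the look does not fall on the planned event count. If the named function and the printed numbers disagree, it is not settled in advance which of them supplies that boundary.

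**Working it through.** **Inputs.** One-sided alpha 0.025, 80% power, HR 0.50, 72 events and a look at 41 events (Sample size {14}); 57% and non-binding futility (Interim analyses {21b}); 2:1 allocation (Trial design {8}). The information fraction is t = 41/72 = 0.5694, printed as 57%.

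**Step 1: is Table 2 coherent in itself?** Yes. The alpha column sums to 0.0046 + 0.0204 = 0.025 and the beta column to 0.0370 + 0.1630 = 0.20. Integrating the bivariate normal with correlation √t, ignoring the futility bound, the rounded boundaries 2.60 and 1.99 give 0.0047 + 0.0204 = 0.0251 one-sided. That is 0.025 within rounding.

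**Step 2: the named function.** Lan-DeMets O'Brien-Fleming spending is α(t) = 2[1 − Φ(z₁₋α/₂ / √t)]. With α = 0.025 the constant is 2.2414.

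- At t = 41/72: 2.2414 / 0.7546 = 2.970, so α(t) = 0.00298 and Z = 2.750.
- At t = 0.57: α(t) = 0.00299 and Z = 2.749. Rounding of t is therefore not the explanation.
- Alpha left for the final test: 0.025 − 0.0030 = 0.0220. Solving for the final bound gives Z = 1.98 (1.977).
- This function would spend 0.0046 only at t = 0.626, about 45 events.

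**Step 3: which function gives the printed figures?** All at t = 0.57; each spending function is also applied to beta 0.20:

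| Candidate | Interim alpha | Interim Z | Final Z | Same function on beta 0.20 |
|---|---|---|---|---|
| Table 2 | 0.0046 | 2.60 | 1.99 | 0.0370 |
| Lan-DeMets O'Brien-Fleming, one-sided 0.025 | 0.0030 | 2.75 | 1.98 | 0.0896 |
| The same at two-sided 0.05, halved | 0.0047 | 2.60 | 1.99 | 0.1325 |
| Classical O'Brien-Fleming | 0.0042 | 2.63 | 1.99 | – |
| Hwang-Shih-DeCani (−4) | 0.0041 | 2.64 | 1.99 | 0.0328 |
| Power family, exponent 3 | 0.0046 | 2.60 | 1.99 | 0.0370 |

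For the power family: 0.025 × 0.57³ = 0.00463 and 0.20 × 0.57³ = 0.03704. The remainders are 0.0204 and 0.1630. Solving for 80% power gives a drift of 2.837 and a futility bound of 2.837 × √0.57 − 1.786 = 0.36. All the printed figures are recovered.

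**Step 4: size at the planned look.** Under 2:1 allocation, log HR has standard error 1/√(41 × 2/9) = 1/3.018.

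- Observed HR at the boundary: exp(−2.60/3.018) = 0.423 for Table 2; exp(−2.75/3.018) = 0.402 for the named function.
- Under HR 0.50 the drift at 72 events is ln 2 × √(72 × 2/9) = 0.693 × 4 = 2.77, and at the interim 2.77 × √0.5694 = 2.09.
- Probability of crossing: 1 − Φ(2.60 − 2.09) ≈ 0.31; 1 − Φ(2.75 − 2.09) ≈ 0.255.

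**Step 5: size when the look is off plan.** Interim efficacy Z recomputed at the actual count, out of 72:

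| Events at look | Named function | Power family, exponent 3 |
|---|---|---|
| 38 | 2.87 | 2.68 |
| 41 | 2.75 | 2.60 |
| 44 | 2.64 | 2.53 |

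**The case against.** The strongest defence is that the document prints only one set of boundaries and tells the analyst to use it. A value of 2.75 appears nowhere. At exactly 41 events, 2.60 can fairly be read as the operative cut-off. This stands, and it limits the harm. It does not help at another event count, where Table 2 has no entry and the only rule in the text is the named function.

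A second defence is that O'Brien-Fleming spending at two-sided 0.05, halved, gives both printed Z-values to two decimals. This stands in part. It spends 0.0047 / 0.0203 and not 0.0046 / 0.0204, and the text does not state this variant. Its failure to give 0.0370 is weaker evidence, because O'Brien-Fleming is named for alpha only and no beta-spending function is named. The power-family origin is therefore the best fit, but it remains an inference.

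Three stronger readings are tempting, and the documents do not support them:

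- **Type I error is inflated.** Inflation would need boundaries taken from different rules, such as 2.60 at the interim with a final value below 1.99. The protocol prescribes no such mixture.
- **General methods adds a third rule.** It says "The primary endpoint hypothesis tests will be 2-sided with a significance level of" 0.05. That leaves 0.025 in the efficacy tail, in line with Sample size {14}, and it states no critical value of 1.96. At most the one-sided and two-sided wording is loose.
- **A fixed share of trials would get opposite decisions.** This assumes an analyst who sets aside the instruction to use Table 2 at the planned look.

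**Conclusion.** The point holds as a mismatch between a named method and its stated threshold. The Lan-DeMets O'Brien-Fleming function at one-sided 0.025 and 41/72 events gives 0.0030 / 2.75 and 0.0220 / 1.98; Table 2 gives 0.0046 / 2.60 and 0.0204 / 1.99.

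At the planned look the gap is modest: 0.15 on the Z scale, about 0.02 in observed hazard ratio, and about 5 percentage points in crossing probability. Off plan it is 0.19 at 38 events and 0.11 at 44. Overall alpha control is not in question if Table 2 is applied as printed.

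The hazard-ratio and crossing figures assume proportional hazards, the usual 2/9 information per event under 2:1 allocation, and an approximately normal test statistic. The boundary values themselves need only alpha, t and the spending function.

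**What to change.** Settle one rule before any unblinded look, in one of two ways:

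1. Keep Table 2 and name the function that generated it in both Sample size {14} and Interim analyses {21b}. If the sponsor's design file confirms it, that is the power family with exponent 3, for alpha and for beta.
2. Keep Lan-DeMets O'Brien-Fleming, replace the superiority columns with 2.75 / 0.0030 and 1.98 / 0.0220, and recompute the futility bound together with the beta-spending function, which should then be named.

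In either case, add a sentence saying that both bounds are recomputed from the named function at the actual event count.

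The cost is some wording and, under the second option, one small table. The planned 72 events need not change: power at 72 events, ignoring the futility bound, is about 78.7% with Table 2 and 78.9% with the named function.

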### Methods for additional analyses (e.g., subgroup analyses) {20b}

Subgroup analyses for the primary endpoint will be carried out separately for two predefined subgroups in the same manner as described in the relevant section.

These subgroups are:Utrecht stage: early vs. late (<0.25 vs. >0.25).Neurofilament light chain: high vs. low.

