#### Statistical methods for primary outcome

The primary endpoint of this study is a composite of time to death from any cause or respiratory insufficiency (DRI; defined as tracheostomy or the use of non-invasive ventilation for ≥22 h per day for ≥10 consecutive days). For each individual we will calculate the primary endpoint as [date of event/censor – date of randomization]/365.25. An indicator variable will be defined specifying whether the patient was alive or had an event at the end of the study. To test the difference between treatment arms, we will use a likelihood ratio test stratified for the randomization factor “*trial site*” and adjusted for “*TRICALS Risk Profile*” as continuous variable. The TRICALS Risk Profile will be fitted as linear effect. This likelihood ratio test will also be used for sequential monitoring of efficacy during one pre-specified interim analysis. The Kaplan-Meier plots estimating the cumulative event rate will be provided for each treatment group. In case of non-proportional hazards, we will estimate the mean difference in Restricted Mean Survival Time (RMST).

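### Subgroup analyses are planned as separate repeats of the primary treatment test with no treatment-by-subgroup interaction stated, so they do not address whether the effect differs between levels

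*Protocol article*

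**What the plan says.** The section on additional analyses {20b} of the protocol article reads: "Subgroup analyses for the primary endpoint will be carried out separately for two predefined subgroups in the same manner" as the section for that endpoint sets out. Two factors follow. One is Utrecht stage, split at 0.25 into early and late. The other is given as "Neurofilament light chain: high vs. low".

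For the primary endpoint, the section referred to is Statistical methods for primary outcome. There the plan states that "we will use a likelihood ratio test stratified for the randomization factor" of trial site, with the TRICALS risk profile as a continuous linear covariate. The effect tested is treatment alone.

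The only interaction with treatment in the document is treatment by time, in the ALSFRS-R sub-model of the joint model. General methods sets the primary hypothesis tests at two-sided 0.05. Its rule that results are exploratory and carry no inferential statements is written for secondary endpoints, so it does not reach subgroup analyses of the primary endpoint.

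**The concern.** A subgroup analysis is meant to show whether the treatment effect differs between kinds of patient. A test of treatment within one level, set beside the same test in the other, does not answer that. The two p-values depend heavily on how many events each level has, and with 72 events in total each level has few. One level can reach significance and the other miss it when the benefit is the same in both.

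The risk matters here because the trial itself follows from an exploratory genetic subgroup finding in 46 patients. A pattern of apparent benefit only in early stage, or only at one neurofilament level, could be taken up in the same way and wrongly narrow who is thought to benefit.

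**Working it through.** **Inputs from the protocol article**
- Effect size: "we assumed a conservative hazard ratio of 0.50" (Sample size {14}); taken here as the same in both levels.
- Events: 72 for 80% power, and 41 at the interim (Sample size {14}).
- Significance level: "With the use of a one-sided test at the 0.0250 significance level" (Sample size {14}), or two-sided 0.05 in General methods. Both give a critical value of 1.96 in the direction of benefit.
- Allocation: 2:1 (Trial design {8}), so the information per event is (2/3)(1/3) = 2/9.

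**Input not in the document**
- The split of events between levels. I assume 50:50 and show the range to 90:10. Early Utrecht stage is only the first of four stage categories, so an even split should not be presumed.

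**Step 1. Reproduce the plan's own figure.** Schoenfeld events = (1.96 + 0.84)² / [(2/9)(ln 0.5)²] = 73.5, against 72 stated. Power at 72 events = Φ(ln 2 × √(72 × 2/9) − 1.96) = Φ(2.773 − 1.96) = 79.2%. With the group-sequential bounds 2.60 and 1.99 and no futility stop it is 78.7%. The stated 80% is reproduced closely enough to use this formula.

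**Step 2. Power within each level.** Power = Φ(ln 2 × √(D × 2/9) − 1.96), where D is the number of events in the level:
- D = 36: Φ(1.960 − 1.96) = 50.0%
- D = 18: Φ(1.386 − 1.96) = 28.3%
- D = 54: Φ(2.401 − 1.96) = 67.0%

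**Step 3. Chance that exactly one level is significant,** p₁(1 − p₂) + p₂(1 − p₁), at 72 events and a uniform hazard ratio of 0.50:

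| Event split | Power, larger level | Power, smaller level | Exactly one | Both | Neither |
|---|---|---|---|---|---|
| 50:50 | 50.0% | 50.0% | 50.0% | 25.0% | 25.0% |
| 60:40 | 57.4% | 41.8% | 51.2% | 24.0% | 24.8% |
| 75:25 | 67.0% | 28.3% | 57.4% | 19.0% | 23.6% |
| 90:10 | 74.9% | 13.9% | 67.9% | 10.4% | 21.6% |

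Simulation with 1,000,000 draws per split agreed. Further results:
- Among simulated trials that win overall at 72 events (critical value 1.99), exactly one level is significant in 58% (50:50) to 82% (90:10).
- With 41 events the unconditional figure is 43% to 51%.
- If both factors split evenly and independently, at least one of them shows the pattern in about 67% of trials.

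**Step 4. The interaction test under the same conditions.** At two-sided 0.05 it falsely signals a difference in 5% of trials per factor, whatever the split. Its standard error for the log ratio of hazard ratios with 36 + 36 events is √(1/8 + 1/8) = 0.5, so its power is:
- two-fold ratio: Φ(0.693/0.5 − 1.96) = 28%
- three-fold ratio: Φ(1.099/0.5 − 1.96) = 59%
- four-fold ratio: Φ(1.386/0.5 − 1.96) = 79%

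**Step 5. Site strata.** A 36-event level spread over 14 sites (Study setting {9}) has 36/14 = 2.6 events per stratum on average; with the 15 sites in the Abstract it is 2.4. Strata with patients at risk in only one arm add nothing to the comparison. I have not quantified this loss. Adjustment for the risk profile may work in the other direction, so the powers above are approximate.

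**The case against.** The sentence in {20b} can be read in two ways. The two items listed are factors, not levels, so carrying the analyses out separately may mean only that the factors are taken one at a time. The article never says that the test is run inside each level. On that reading, what remains is an unnamed interaction term, which a condensed article may leave to an unseen analysis plan. Separate estimates and an interaction test are also compatible, and nothing excludes the latter.

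The ambiguity is real, and within-level testing is an inference, though a natural one. It does not remove the point. On either reading the method is stated to be that of the primary analysis, which tests treatment alone, so the stated method contains no comparison between levels. That is a choice made in the text and not mere silence. An analysis plan may add an interaction, but it would be adding to what this text describes.

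A second objection is that 50% measures a misreading and not a planned decision. This stands. The protocol gives no rule that treats one significant and one non-significant level as heterogeneity, and the stopping-rule table assigns no alpha to subgroups. A reader might infer that the plan would produce a false subgroup claim in half of trials; the document does not support that.

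**Conclusion.** The point holds as a weakness in the stated method. The subgroup analyses, as described, do not address whether the effect differs between levels. Under a uniform hazard ratio of 0.50 at 72 events, they would show significance in exactly one level about 50% of the time with an even split, 57% at 75:25 and 68% at 90:10.

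These figures rest on an assumed event split, on testing within each level, and on each level being read as significant or not at two-sided 0.05. They give the chance of a misleading pattern per factor. The primary result, its error control and the sample size are unaffected, so a stronger conclusion about the trial's validity is not warranted. The missing cut-off for neurofilament light is a detail that an analysis plan may supply, and I do not count it against the document.

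**What to change.** In {20b}, state that for each factor in turn the subgroup variable and the treatment-by-subgroup interaction are added to the primary model, keeping site stratification and the continuous TRICALS risk profile, in the full efficacy population. Report the ratio of hazard ratios with its 95% CI. Show the hazard ratio and CI in each level from the same model, as description, with no claim of significance within a level. Keeping all patients in one model also leaves about 72/14 = 5.1 events per site stratum in place of 2.6.

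The cost is wording only; conduct, sample size and alpha do not change. Two limits should be written down:
- The interaction has low power, about 28% for a two-fold ratio at 36 + 36 events. It is to be read as an estimate, and a non-significant result is not proof of a uniform effect.
- Utrecht stage and the TRICALS risk profile both derive from the ENCALS model, so a difference by stage cannot be cleanly separated from a difference by prognosis.

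Modelling neurofilament light as continuous is an option, but it is a preference and not part of this correction.

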### Methods in analysis to handle protocol non-adherence and any statistical methods to handle missing data {20c}

Missing data in any of the outcomes will not be imputed.

### Plans to give access to the full protocol, participant level-data and statistical code {31c}

Non-identifiable patient-level data may be available on request.

## Oversight and monitoring

### Composition of the coordinating center and trial steering committee {5d}

The UMC Utrecht is the coordinating center, but coordination of the trial and of trial sites is performed by the sponsor, TRICALS. There are weekly meetings with the lead investigator, the medical reviewer, the project manager and clinical research associate. The latter two are also part of the sponsor safety committee. There is no trial steering committee, as tasks of the trial steering committee have been delegated to the Data Safety Monitoring Board (DSMB).

### Composition of the data monitoring committee, its role and reporting structure {21a}

A DSMB has been established to provide oversight of safety and efficacy considerations during the conduct of the current study and to provide advice to the sponsor regarding actions the committee deems necessary for the continued protection of patient enrolled in the study. The DSMB is an independent multidisciplinary group that, collectively, has experience in the management of patients with ALS, and in the conduct and monitoring of randomized clinical trials. DSMB members are independent of the sponsor and all investigational study sites.

The DSMB will provide recommendations about stopping or continuing the trial. To contribute to enhancing the integrity of the trial, the DSMB may also formulate recommendations relating to the selection, recruitment, and retention of patients, their management, improving adherence to protocol-specified regimens and retention of patients, and the procedures for data management and quality control. The DSMB may decide to prematurely terminate the trial for safety when the interim safety analysis indicates that serious adverse effects occur significantly more often in one group than in the other group, or when there is evidence for accelerated disease progression in the treatment arm compared to the placebo arm. Additionally, the DSMB may decide to prematurely terminate the trial for efficacy when any of the stopping rules as described previously are met.

The advice(s) of the DSMB will only be sent to the sponsor of the study. Should the sponsor decide not to fully implement the advice of the DSMB, the Sponsor will send the advice to the reviewing IRB, including a note to substantiate why (part of) the advice of the DSMB will not be followed.

